### Data collection, management, and analysis

Data will be entered using EpiData software designed for this study. All data will be collected, typed, and analyzed by a statistician, who will be blinded during the trial. The main investigators will check the data every 2 weeks to ensure the quality. All statistical analyses will be performed using SPSS 20.0. Descriptive data will be presented as mean ± standard deviation. Considering that age may be a potential factor influencing the outcome measurement, a covariance analysis will be used to compare the effects between two groups. A *t* test will be used to compare changes in parent outcome measures in the two groups. Multiple linear mixed models will be used to analyze the relationships between the risk factors and the outcome measures. An intention-to-treat analysis will be used if participants are lost to follow-up. All statistical tests will be performed at a significance level of 0.05.

The parents will also be informed of this crucial aspect, and a member of the intervention team will be available any time the parents may need further information or clarification during the study period.

An interim analysis will be performed by the statistician on the primary endpoint; the statistician will be blinded for treatment allocation and will report to the main investigators. The main investigators will discuss the results of the interim analysis with the monitoring board. However, the trial will be terminated in case of harm. The criterion for stopping the trial for harm is as follows: a statistically significant difference in the primary outcome between the intervention group and a reasonable suspected causal relationship between the intervention and adverse events.

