### Study design

Children with CHD who are planning to perform a cardiac catheterization procedure will be recruited from the Department of Pediatric Cardiology, Xinhua Hospital affiliated to Shanghai Jiao Tong University School of Medicine, China.

The study will be implemented at the Shanghai Jiao Tong University School of Medicine. Before participation in the study, parents/legal guardians will be asked to sign a written informed consent. First, patients who meet the inclusion criteria will be recruited for the study through echocardiography results. Second, patients will undergo baseline evaluations including motor abilities, cardiac function, modified Ross score, sound of speed at the tibia, and functional independence level, and their parents will complete three questionnaires about their anxiety levels, quality of life, and caregivers’ burden. Children with CHD will be allocated by a physician using computer-generated block randomization into two groups: an intervention group and a control group after the catheterization process. The allocations will be concealed in sequentially numbered, opaque, sealed envelopes through a signature across the sealing point. A trained research assistant, who will be blinded to the allocation, will enroll patients and assign them to interventions. All evaluations will be carried out by the evaluation team. Another team, composed of experienced pediatric physiotherapists, will teach parents the home-based exercises, remind them to perform the exercises, and provide valuable information about the details of the exercises. The evaluation team will be blinded in this program; however, the intervention team will not be blinded, as they must communicate with parents and offer informed consent in order to obtain the parents’ signatures. The intervention group will receive a home-based exercise program, while the control group will only receive home-based education (see Fig. 1). All children and parents will be evaluated by the trained evaluation team before the procedure and 1, 3, and 6 months after the cardiac catheterization. Micro Message Public Platform dissemination and collaboration with staff of the Department of Pediatric Cardiology was established to facilitate enrollment to reach the target sample size. All parents will be added into a CHD group of the Micro Message Platform created by the intervention team to remind them to bring their children for clinic visits in order to promote patient retention.

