### Primary outcome measures

#### Motor ability quotient

The Peabody Developmental Motor Scales, 2nd edition (PDMS-2) [28] will be used to assess each child’s motor development. The PDMS-2 is a performance-based tool used to assess motor development in both clinical and research settings. The PDMS-2 measures development in two domains, gross motor and fine motor, and it incorporates both quantitative and qualitative rating criteria. It consists of six sub-tests: reflexes, stationary, locomotion, object manipulation, grasping, and visual-motor integration. Sub-test scores are standardized by age and combined to calculate gross, fine, and total motor quotients. The raw scores for each of the sub-tests will be converted to age-equivalent scores, percentile ranks, standard scores, and composite scores. The PDMS-2 is a valid and reliable tool to assess motor development in children, and has excellent intra-rater reliability.

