### Sample measurement

GPower 3.1.9.2 will be used to perform the power calculations. The motor quotient of the PDMS-2 will be our primary outcome measurement.

The results of our pilot study showed that after 6 months of intervention, the motor quotient of the intervention group with patent ductus arteriosus on average was (94.33 ± 11.29), and that of the control group was (84.67 ± 6.11); therefore, the effect size was 1.06. Thus, as the α will be 0.05 and the β will be 0.05, each group should recruit 24 patients. Considering 10% potential attrition, 27 patients in each group with patent ductus arteriosus will be recruited.

The motor quotient of the intervention group with pulmonary stenosis on average after 6 months of intervention was (101.00 ± 9.90), and that of the control group was (89.00 ± 1.41); therefore, the effect size was 1.70. Thus, as the α will be 0.05 and the β will be 0.05, each group should recruit 11 patients. Considering 10% potential attrition, 13 patients in each group with pulmonary stenosis will be recruited.

The motor quotient of the intervention group with ventricular septal defect on average after 6 months of intervention was (95.00 ± 8.54), and that of the control group was (90.50 ± 7.78); therefore, the effect size was 0.55. Thus, as the α will be 0.05 and the β will be 0.05, each group should recruit 87 patients. Considering 10% potential attrition, 96 patients in each group with ventricular septal defect will be recruited.

The motor quotient of the intervention group with atrial septal defect on average after 6 months of intervention was (99.67 ± 5.43), and that of the control group was (90.80 ± 5.72); therefore, the effect size was 1.59. Thus, as the α will be 0.05 and the β will be 0.05, each group should recruit 12 patients. Considering 10% potential attrition, 14 patients in each group with atrial septal defect will be recruited.

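### The baseline motor quotient is not named as a covariate and parent outcomes use a t test on change, which costs precision but causes no bias

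*Protocol article*

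**What the plan says.** Under Data collection, management, and analysis, the protocol article describes three methods.

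- Group comparison: "Considering that age may be a potential factor influencing the outcome measurement, a covariance analysis will be used to compare the effects". Age is the only reason and the only covariate given. The sentence is not tied to a particular outcome, and it does not say whether follow-up values or changes are analysed.
- Parent outcomes: a *t* "test will be used to compare changes in parent outcome measures in the two groups".
- Mixed models: "Multiple linear mixed models will be used to analyze the relationships between the risk factors and the outcome measures". These are assigned to risk factors and not to the treatment comparison.

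Under Sample measurement, the primary outcome is fixed: "The motor quotient of the PDMS-2 will be our primary outcome measurement". Under Motor ability quotient, the scoring is described: "Sub-test scores are standardized by age and combined to calculate gross, fine, and total motor quotients".

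Under Study design, the baselines are collected: "patients will undergo baseline evaluations including motor abilities, cardiac function, modified Ross score, sound of speed at the tibia, and functional independence level". In the same section, parents complete three questionnaires at baseline, on anxiety, quality of life and caregiver burden.

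**The concern.** A covariate improves a randomised comparison in proportion to how well it predicts the outcome. For the motor quotient, age-standardised scoring is designed to remove the variation that age would explain. The child's own quotient before the procedure would normally be a much better predictor. It is available for every child, yet it is not named.

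For parents, a t test on change subtracts the whole baseline score, which amounts to fixing the baseline slope at 1. Covariance analysis estimates the slope and is more precise whenever the correlation between baseline and follow-up is below 1.

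Precision on the primary outcome is at stake, and so is precision on the parent outcomes. The latter carry the trial's aims on parental anxiety, caregiver burden and quality of life, and the article gives no sample size calculation for them. Protection against a chance imbalance at baseline is also at stake.

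**Working it through.** **1. The plan's own sample size.** Inputs are from Sample measurement: pilot means and SDs at 6 months, α 0.05, β 0.05. Effect size d = difference / √((s₁² + s₂²)/2).

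For ventricular septal defect: √((8.54² + 7.78²)/2) = 8.17, and d = (95.00 − 90.50)/8.17 = 0.551. A two-sided two-sample t test (noncentral t) at 95% power needs 87 per group, as stated.

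The other three lesions give d = 1.064, 1.697 and 1.590, with 24, 11 and 12 per group, as stated (the first becomes 25 if d is rounded to 1.06). With attrition the stated groups are 27 + 13 + 96 + 14 = 150 per arm, or 300 in total.

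The sample size is therefore that of an unadjusted comparison of 6-month means, with no covariate in it.

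**2. Assumptions for the next steps.** The baseline to follow-up correlation r is not in the document; I take 0.3, 0.5 and 0.7. Baseline and follow-up variances are taken as equal, with the same r in both arms. Variances are relative to a comparison of follow-up values without baseline (= 1):

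- covariance analysis on baseline: 1 − r²
- change score: 2(1 − r)
- change score relative to covariance analysis: 2(1 − r)/(1 − r²) = 2/(1 + r)

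**3. Primary outcome, baseline quotient added.**

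| r | 1 − r² | Variance cut | Per group, ventricular septal defect | Power at 87 per group |
|---|---|---|---|---|
| none | 1.00 | 0% | 87 | 95.0% |
| 0.3 | 0.91 | 9% | 80 | 96.6% |
| 0.5 | 0.75 | 25% | 66 | 98.6% |
| 0.7 | 0.51 | 49% | 45 | 99.9% |

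Across all lesions, 150 × 0.9 = 135 children per arm remain. The effect detectable with 95% power is (1.960 + 1.645) × √(2/135) × √(1 − r²): 0.44 SD without baseline, and 0.42, 0.38 and 0.31 SD at the three values of r.

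**4. Primary outcome, age alone.** If age keeps a correlation of 0 to 0.2 with the age-standardised quotient (assumed), the variance cut is 0 to 0.2² = 4%, and 87 becomes 84 at best (87 × 0.96 = 83.5).

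**5. Parent outcomes.**

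| r | Change score, 2(1 − r) | Covariance analysis, 1 − r² | Ratio 2/(1 + r) | Excess variance of change score |
|---|---|---|---|---|
| 0.3 | 1.40 | 0.91 | 1.54 | 54% |
| 0.5 | 1.00 | 0.75 | 1.33 | 33% |
| 0.7 | 0.60 | 0.51 | 1.18 | 18% |

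Below r = 0.5 the change score is less precise than the follow-up score alone.

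**6. Chance imbalance, as an illustration.** Suppose the arms differ by 0.2 SD at baseline and r = 0.6. A follow-up comparison without baseline carries 0.6 × 0.2 = 0.12 SD of that gap. A change score over-corrects by (1 − 0.6) × 0.2 = 0.08 SD. Covariance adjustment removes both.

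**The case against.** The strongest reply is that this is a condensed article and a full covariate list may sit in an analysis plan that is not shown. The text gives age as a reason; it does not say that age is the only covariate. That stands: a reader might infer that baseline is excluded from the primary model, but the text supports only that it is not named. The reply does not reach the parent outcomes, where the t test on change is stated outright.

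Nor does the article say what the covariance analysis is applied to. If it is applied to change in the quotient, the baseline is already used. The gain from adding it as a covariate is then the smaller one of the parent case: a factor of (1 + r)/2, or 35%, 25% and 15% less variance at r = 0.3, 0.5 and 0.7.

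A reader might also infer that age adjustment is a mistake. It is not. The sentence can cover echocardiographic dimensions, tibial speed of sound and functional independence in children aged 0 to 5 years. None of these is described as age-standardised, and age is a sensible covariate for them. For the quotient it is harmless.

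A third tempting reading is that the baselines are wasted. For parents this is wrong, because a change score uses each baseline, only less efficiently.

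Finally, under randomisation both a comparison of follow-up values and a t test on change are unbiased, and their standard errors already allow for chance imbalance. The planned number gives its stated power without any covariate. This also stands. It limits the point to efficiency and does not remove it: the 95% power rests on pilot effects of 0.55 to 1.70 SD, and the parent outcomes have no sample size calculation in the article to rest on.

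**Conclusion.** The point holds as one of precision. Age, the only named covariate, is likely to add little for the motor quotient, while the baseline quotient is collected and not named. Adding it would cut the variance by 9% (r = 0.3), 25% (r = 0.5) or 49% (r = 0.7) relative to follow-up values analysed without it. For parents, the stated test on change has 54%, 33% or 18% more variance than covariance analysis at the same correlations.

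The sizes rest on an assumed r and on equal variances at the two times. With equal variances, the direction for parents holds for every positive r below 1. A reader might go further and conclude that the estimates are biased or the sample size invalid. Neither follows: the stated methods are unbiased under randomisation, and the sample size reproduces as an unadjusted comparison.

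**What to change.** - For the motor quotient and the other child outcomes, name the baseline value of the same outcome as a covariate in the group comparison. Age may stay, and is most useful for measures that are not age-standardised.
- For anxiety, quality of life and caregiver burden, replace the t test on change by covariance analysis of the follow-up score on arm, with the baseline score as covariate.

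This is a sentence or two in the analysis section. It uses data already scheduled for collection, runs in the SPSS software already planned, and leaves the sample size unchanged. The one real constraint is timing. Recruitment is under way and an interim analysis of the primary endpoint is planned, so the change should be a dated amendment made before any unblinded look at the data. If an unshown analysis plan already names the baseline quotient, only the parent outcomes need changing, and the article's wording on the child comparison can be aligned with it.

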### Withdrawal criteria and management

Children with CHD and their families will be allowed or be asked to withdraw from the study in the event of the following:The child and his/her family make such a request.The child has an adverse effect/event related to participation in the study.

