### Control group

The intervention team will explain the children’s evaluation results and share home-based exercise education with parents at baseline assessments. Home-based physical activity education will be given to the parents, but they will not receive the rehabilitation guide.

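### Intention-to-treat is made conditional on loss to follow-up, and related adverse events can end study participation, so outcomes may be lost unequally between arms

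*Protocol article*

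**What the plan says.** Three statements in the protocol article bear on who is analysed.

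- **Analysis set** (Data collection, management, and analysis): "An intention-to-treat analysis will be used if participants are lost to follow-up". No other sentence defines the primary analysis population.
- **Withdrawal** (Withdrawal criteria and management): participants "will be allowed or be asked to withdraw from the study in the event of the following". Two triggers are then listed. One is a request by the child and family. The other is this: "The child has an adverse effect/event related to participation in the study". The section does not say whether a withdrawn child is still assessed.
- **Comparison** (Data collection, management, and analysis): "a covariance analysis will be used to compare the effects between two groups", with age as the reason given. Mixed models appear for another purpose: "Multiple linear mixed models will be used to analyze the relationships between the risk factors and the outcome measures".

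The primary outcome is fixed under Sample measurement: "The motor quotient of the PDMS-2 will be our primary outcome measurement". Assessments are planned before the procedure and at 1, 3 and 6 months after it. The arms differ in exposure to the exercises. Under Control group: "Home-based physical activity education will be given to the parents, but they will not receive the rehabilitation guide".

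**The concern.** Intention-to-treat means analysing every randomised child in the allocated arm. It should hold whether or not anyone is lost, and it matters as much for families who stay in follow-up but do not do the exercises. That is a realistic case here: the programme asks parents for 30 minutes on at least 5 days a week for 6 months. The sentence as written does not cover it.

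The withdrawal rule adds a second problem. A related adverse event is a reason to leave the study, so 1-, 3- and 6-month scores may not be collected after it. Only the exercise arm receives the rehabilitation programme, so events related to participation are likely to fall mainly there. If those children would have scored below the rest of their arm, the exercise mean would be taken over children who tolerated the programme, and the comparison would favour the intervention.

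**Working it through.** **1. The plan's own figures.** For ventricular septal defect, Sample measurement gives 95.00 ± 8.54 against 90.50 ± 7.78.

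- Difference = 95.00 − 90.50 = 4.50.
- Pooled SD = √[(8.54² + 7.78²)/2] = √66.73 = 8.17.
- Effect size = 4.50/8.17 = 0.55, as stated.
- A two-sided t test with α 0.05 and power 0.95 needs 87 per group, as stated.
- The four recruitment figures sum to 27 + 13 + 96 + 14 = 150 per group, or 300 in all, as stated.

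These sample-size figures are not in dispute. The 10% attrition allowance is not split by arm or by reason.

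**2. The withdrawal and analysis sections side by side.**

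- *A withdrawn child counts as lost to follow-up.* Intention-to-treat is then invoked, but the child may have no score after withdrawal. A covariance analysis of available scores omits that child, and the article does not say how the child enters.
- *A withdrawn child does not count as lost.* Nothing in the stated rule then calls for intention-to-treat on that child's account.
- *Nobody is lost, but some families do not exercise.* The condition is not met, so the analysis set is left open.

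In none of the three cases does the text secure the analysis of all randomised children as allocated.

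**3. Possible size, by assumption.** Let a fraction q of the exercise arm leave, and let those children have scored k SD below the full arm's mean. Take control losses as unrelated to outcome. The mean of those remaining exceeds the full-arm mean by

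shift = q × k/(1 − q) SD.

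For example, with q = 0.10 and k = 1.0, the shift is 0.10/0.90 = 0.111 SD, and 0.111 × 8.17 = 0.91 points. The last column is the two-sided rejection rate when there is no effect. It uses a normal approximation, with 150 controls and 150(1 − q) exercise children.

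| q | k | Shift (SD) | Points | Share of 4.5 | Rejection rate, no effect |
|---|---|---|---|---|---|
| 2% | 0.5 | 0.010 | 0.08 | 2% | 0.051 |
| 2% | 1.0 | 0.020 | 0.17 | 4% | 0.054 |
| 5% | 0.5 | 0.026 | 0.21 | 5% | 0.056 |
| 5% | 1.0 | 0.053 | 0.43 | 10% | 0.073 |
| 10% | 0.5 | 0.056 | 0.45 | 10% | 0.075 |
| 10% | 1.0 | 0.111 | 0.91 | 20% | 0.155 |
| any | 0 | 0 | 0 | 0% | 0.050 |

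The 10% rows are an upper scenario: they treat the whole attrition allowance in the exercise arm as outcome-related. The values of q and k are assumptions, since the documents give neither.

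**The case against.** The strongest reply is that the sentence on intention-to-treat protects against this very case. A child who withdraws is most naturally counted as lost, and the sentence then calls for intention-to-treat. No per-protocol set is named and no passage excludes withdrawn or non-compliant children. A reader might infer that the exercise arm's poor responders are removed from the primary analysis, but the documents do not support that. Withdrawal is allowed or asked for, not automatic. Nothing links an adverse event to a lower motor quotient, and the Harms section expects no risk in either group.

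A reader might also infer that a covariance analysis cannot be intention-to-treat. That goes too far. It can be, if missing scores are handled suitably, and the method for missing data may stand in an analysis plan that is not shown. Its absence from the article is not counted here. Retention is also partly addressed, through visit reminders to all parents and help with scheduling assessments.

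These replies remove any claim of a demonstrated bias. They do not mend the conditional wording. Nor do they settle whether children withdrawn for a related event are still assessed. A good missing-data method is a weaker remedy than collecting the scores.

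**Conclusion.** The point holds as a fault in two stated rules, not as proof of bias. Intention-to-treat is worded as a contingency when it should be unconditional, and the withdrawal rule can end outcome collection for a reason likely to arise mainly in one arm.

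The size depends wholly on the assumed fraction leaving and their assumed deficit: about 0.1 to 0.9 motor-quotient points over 2% to 10% leaving and 0.5 to 1.0 SD, and none if leavers do not differ. At the low end this is negligible. At the upper end it is a fifth of the difference planned for ventricular septal defect, and the false-positive rate would be about 15% where 5% is intended. A bias in favour of the intervention is plausible but not established. The change is worth making because it is cheap and removes the question.

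**What to change.** 1. Replace the conditional sentence with a statement that the primary analysis includes all randomised children in their allocated arm, whatever their compliance or follow-up.
2. Reconcile the withdrawal and analysis sections by separating stopping the exercises from leaving the study. Children who stop exercising stay in the 1-, 3- and 6-month assessments unless the family withdraws consent. The rule on when exercises stop is not altered.
3. Make the group comparison use every available post-baseline score. One option is the type of linear mixed model that the article already names for risk factors, with baseline, arm, visit and arm by visit, reading off the 6-month contrast. This is optional. It is valid under missing-at-random, and it would not by itself remove bias if leavers' unseen scores are worse than their observed ones predict. Step 2 therefore matters more.

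The cost is protocol wording, a few more follow-up visits for children who have stopped exercising, and a possibly slightly smaller estimate because those children are included.

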### Data monitoring and auditing

A monitoring board, including independent assessors (not involved in the study) from the Shanghai Jiao Tong University School of Medicine, will review all data and can conduct an audit of the trial at any time.

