### Confidentiality

Only the main investigators will be allowed back-end EpiData software entry with passwords. All children with CHD will be identified by sex, birth date, and evaluation date, and will be assigned a trial number during and after the trial in accordance with personal data protection laws.

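### The interim comparison of the primary endpoint is reported to the main investigators before the monitoring board, so those running the trial may learn the interim effect while it continues

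*Protocol article*

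**What the plan says.** The section Data collection, management, and analysis of the protocol article sets out the interim look in three steps.

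- The analysis: "An interim analysis will be performed by the statistician on the primary endpoint".
- The first recipient: "the statistician will be blinded for treatment allocation and will report to the main investigators".
- The second recipient: "The main investigators will discuss the results of the interim analysis with the monitoring board".

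The same section gives the criterion for stopping for harm as "a statistically significant difference in the primary outcome between the intervention group and a reasonable suspected causal relationship between the intervention and adverse events".

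Two statements describe what else the main investigators do during the trial. On data checks: "The main investigators will check the data every 2 weeks to ensure the quality". Under Confidentiality: "Only the main investigators will be allowed back-end EpiData software entry with passwords".

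Under Data monitoring and auditing, a monitoring board that includes independent assessors "will review all data and can conduct an audit of the trial at any time".

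**The concern.** Comparative interim results are normally kept from the people who conduct a trial, because knowledge of a trend can change how the rest of it is run. Here the blinded person is the analyst, and the recipients of the result are the investigators. Blinding the analyst protects the analysis. It does not protect trial conduct.

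This trial has reason to care. The home programme depends on effort: it is tailored to each child, taught one-on-one until the parents have mastered it, and backed by reminders once or twice a week. The team delivering it is unblinded. If those in charge know a trend, retention effort, emphasis in coaching or attention to particular data queries could shift. The final analysis could neither detect nor correct such a shift.

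**Working it through.** No figure in the plan settles this point. It turns on four questions, each answered from the text.

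**1. In what order does the interim result travel?** Data collection, management, and analysis gives statistician, then main investigators, then monitoring board. The article describes no direct route for the interim result from statistician to board. This is a stated rule, so it is not a detail left open for an unseen analysis plan. A plan that sent the result only to the board would contradict it.

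**2. Is the look comparative or pooled?** The analysis is of the primary endpoint. The harm criterion requires a significant difference in that endpoint. Its wording names only the intervention group; I read it as intervention against control, since no other comparison makes sense in a two-arm trial. Data pooled over arms cannot supply that test, so the interim analysis must compare arms.

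**3. Are the main investigators blind?** Study design blinds the enrolling research assistant and the evaluation team and says that the intervention team is not blind. Data collection, management, and analysis blinds the statistician. No section blinds the main investigators.

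**4. What could they learn?** A blinded statistician can supply only coded arms. A coded comparison still shows the size and significance of the difference. To apply the harm criterion, someone must also know which arm is worse and must link adverse events to the intervention. In practice that requires the code. So the size of the effect may be disclosed, and probably its direction. This is an inference from the stated rules; the article does not say it in words.

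**How many children would follow the look?** The article does not time the look, so this can only be illustrated. The planned total reproduces from Sample measurement: 2 × (27 + 13 + 96 + 14) = 300. Before the 10% allowance for attrition it is 2 × (24 + 11 + 87 + 12) = 268. The number of analysable outcomes still to come after a look at fraction f is 268 × (1 − f):

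| Assumed timing f | Outcomes still to come |
|---|---|
| 0.25 | 268 × 0.75 = 201 |
| 0.50 | 268 × 0.50 = 134 |
| 0.75 | 268 × 0.25 = 67 |

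These count children exposed to a possible change in conduct. They do not measure bias, and the point does not depend on them.

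**The case against.** **The board has its own access.** A reader might infer that adverse events have no route to the board, or that decisions on harm are filtered through the investigators. The article does not support that. Data monitoring and auditing lets the board review all data and audit at any time, and that is not limited to the primary endpoint. Only the interim result reaches the board second-hand. The objection disposes of the safety argument but leaves the disclosure to the investigators untouched.

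**The report may be coded.** The article does not say what the report contains or whether arms are identified, so it would be too strong to state as fact that the investigators see the unmasked effect. This stands as a limit on the wording. It does not remove the concern, because coding hides neither size nor significance and the harm criterion would probably force decoding.

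**Roles are separate.** Tailoring, coaching and reminders belong mainly to the intervention team, which is unblinded whatever the interim shows. A separate blinded team assesses outcomes, and allocation is concealed. No section says that the main investigators coach, recruit or assess. Any influence would therefore be indirect, through their leadership of the trial. It is a plausible risk that the documents do not demonstrate.

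**Data access is described narrowly.** Restricted back-end entry does not mean that the investigators alone handle the data, since the statistician collects and enters them. The 2-weekly check is for quality, and nothing says that it compares arms. I do not claim that it does; it shows only that the investigators stay active in the trial after the look.

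**A head-count is tempting.** A reader might say that at least 150 of 300 children would provide primary data after the look (300 × 0.5). That assumes a half-way look and ignores the 10% attrition allowance. On the analysable target the half-way figure is 134.

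**Conclusion.** The point holds as one of trial governance. The article fixes a reporting line that hands a comparative interim result to the main investigators before the board and does not keep those investigators blind. They may learn the size, and probably the direction, of the interim effect while the trial is still running.

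This rests on two readings: that the harm criterion compares intervention with control, and that applying it needs the direction of the difference. Both follow closely from the text. The size of any bias cannot be derived from the documents. The change is worth making because the harm to conduct, if it occurred, could not be repaired at analysis, and because the remedy is cheap.

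**What to change.** In Data collection, management, and analysis, replace the two statements on reporting with a rule to this effect: the statistician sends the interim report, containing the primary endpoint and adverse events by coded arm, directly and only to the independent members of the monitoring board. Those members may obtain the code if they need it. They return only a recommendation to the main investigators, and no between-arm results are released to the investigators before database lock.

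The report should go to the independent members specifically, because Data monitoring and auditing says only that the board includes independent assessors.

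**Cost.** The statistician, the interim analysis and the board are already planned, and no sample size or significance level changes. The board takes on the handling of closed reports, and the investigators give up sight of interim results. Trial status says that recruitment is already under way, so this is a procedural change during the trial and protects it only if made before the interim analysis.
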